### Outcomes

#### Primary outcome

*Depressive symptom severity* is assessed with the Beck Depression Inventory-II (BDI-II) [54]. BDI-II comprises 21 items assessing the DSM symptoms of the major depression episode during the past 2 weeks. Each question is scored on a 4-point Likert scale ranging from 0 to 3, with higher scores indicating higher depression. The BDI-II manual states that scores between 0 and 13 indicate minimal depression, 14 to 19 indicate mild depression, 20 to 28 indicate moderate depression, and 29 to 63 indicate severe depression [55]. Psychometric strengths such as validity and reliability were supported by numerous studies across many populations and cultural backgrounds [54, 56].

#### Secondary outcomes

*Depressive symptoms severity* is assessed with the Patient Health Questionnaire- 9 [57]. PHQ-9 scale contains nine items that measure the severity of nine depressive symptoms on a 4-point scale during the past two weeks. Each item is rated on a 4-point scale ranging from 0 (not at all) to 3 (nearly every day).

*Depression remission* is measured using The Structured Clinical Interview for DSM-5 Clinician Version [SCID-5-CV; 58], affective module at post measurement and follow-up. SCID-5 is a structured clinical interview used to determine the core diagnoses according to DSM-5 guidelines. Participants are considered remitted when they no longer fulfil diagnostic criteria for a major depression episode.

*Depression response* is assessed based on BDI II scores. To identify responders to treatment we compute the reliable change index. A reliable change index of more than 1.96 will classify a participant as a responder [59].

*Anhedonia severity* is assessed with the Snaith-Hamilton Pleasure Scale [60] SHAPS is a 14-item scale assessing the degree to which a person is able to experience pleasure or the anticipation of a pleasurable experience. Participants respond on a four points scale from strongly disagree to strongly agree. Each "disagree" response receives one point, whereas each "agree" response receives zero points. Thus, the final score ranges from 0 to 14.

*Apathy level* is assessed with the Apathy-Motivation Index [61]. AMI is a 18-item questionnaire used to identify three dimensions of apathy: Behavioural Activation (propensity to initiate goal-directed behaviour), Social Motivation (level of engagement in social interactions), and Emotional Sensitivity (feelings of positive and negative affection). Higher scores indicate greater apathy. Item scores are averaged to get scores for subscales and a total score (range 0–4) [61].

*Anxiety severity* is assessed with the Generalised Anxiety Scale 7 [GAD-7; 62]. GAD-7 is a self-report scale measuring the severity of generalised anxiety disorder (GAD) during the past 2 weeks. It contains seven items related to DSM criteria for anxiety. Participants respond on a 4-point scale. Each item is rated on a 4-point scale ranging from 0 (not at all) to 3 (nearly every day).

*Health and disability level outcome* is assessed with The World Health Organisation Disability Assessment Schedule (WHODAS 2.0) 12 –Self-Report Version WHODAS 12), [63]. WHODAS 12 is a practical, general assessment instrument. It has 6 subscale, each subscale containing two questions from the corresponding subscale in the full version: cognition, mobility, self-care, getting along, life activities and participation. The response options for each item ranged from 0 (none), to 4 (extreme/cannot do). The individual scores in each subscale are calculated by adding the two item scores. The total score ranges from 0–48.

*Adverse and unwanted effects of the experimental intervention* are assessed using the Negative Effects Questionnaire [64]. NEQ is a 20-item scale used to assess the adverse and unwanted effects of psychological treatments. Participants respond on a 5-point Likert-scale about the presence of adverse events during treatment such as symptoms (e.g., stress, shame, anxiety), quality (e.g., confidence regarding treatment and therapy), dependency (e.g., addiction to treatment medicine or therapy), stigma (e.g., feeling ashamed in front of other people), hopelessness, and failure (e.g., when thinking that things could get better) [65].

*The vividness of motor imagery* is assessed using the Vividness of Motor Imagery Questionnaire-2 (VMIQ-2) [66]. The vividness of imagining twelve movements is measured using a Likert scale from 1 (perfectly clear and vivid as you would normally picture the image) to 5 (no image or sensation at all, you are only aware you are “thinking” of the movement). The VMIQ-2 version was found to be as a psychometrically valid questionnaire) [66, 67].

*The level of rewards* is assessed with “The environmental and reward observation scale” (EROS); [68]. EROS consists of 10 items (e.g., “It is easy for me to find enjoyment in my life”), where responses are given on a Likert-type scale ranging from “completely disagree” to “absolutely agree”, on a 4-point scale. A higher score indicates a larger experience of reinforcing events from the environment.

*The level of rumination* is assessed with the Ruminative Response Scale-SV [69]. Participants respond on a 4-point Likert scale ranging from 1 (“almost never”) to 4 (“almost always”). The scale describes different components of the rumination response to depressed mood such as self-focused rumination (e.g., “I can’t stop thinking about some things”), symptom focused rumination (e.g., “I have never been able to distract myself from unwanted thoughts”) or rumination focused on the possible consequences and causes of the mood (e.g., "When I have a problem it will gnaw in my mind for a long time"). Brooding involves self-criticism, whereas reflection is related to more active problem solving.

*Activation and avoidance* is assessed using the Behavioral Activation for Depression Scale—Short Form (BADS-SF) [70]. BADS-SF is a 9-item scale used to assess the activation over the past week. It is organised in activation and avoidance subscales. BADS-SF is used to track when and how participants were activated during BA treatment.

*Working memory* is assessed with a Backward digit span task. Participants are given a series of digits and asked to repeat them backward. The score is based on how many numbers participants are able to repeat. A higher score indicates better working memory. Pairs of the sequences are read aloud to participants. The subsequent set of sequences will be one digit longer if both are successfully repeated and one digit shorter if none of the pair’s sequences is correctly repeated. The following pair of sequences will have the same length if one of the pair’s sequences is incorrectly repeated while the other sequence is correctly repeated [71].

*Executive functioning* is assessed with the verbal fluency test. In the verbal fluency test, participants are asked to say as many words as possible with a given letter (consonant F, A or S) for 1 minute.

*Verb fluency*. In the verb fluency task, participants are asked to produce as many verbs as possible for one minute. The participant’s score in each task is the number of total correct words.

*Acceptability ratings*. Acceptability is measured as satisfaction with the intervention, intention to continue and the intention to recommend the intervention assessed on a 5-points Likert scale. Drop-out rates are analysed as well.

*Affect and behaviour monitoring scale*. Changes in functioning, emotions, behaviour profile, efficacy, and difficulty of simulation are assessed. For each item, the score ranges from 1 (not at all) to 7 (very much).

### Proposed sample size

The sample size was established using G*Power and selecting the difference between two independent means. Forty-four participants per arm will be required to obtain a 90% statistical power. This estimation is based on previous studies targeting robust processes in depressed individuals (rumination) and between-treatment effect size of Cohen’s d = 0.7. Assuming a dropout rate of 20%, 55 patients are required in each treatment arm, resulting in a total of 110 participants.

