### Statistical analyses

Multiple imputation methods will be selected to address the missing data. All randomised patients will be included in intention-to-treat analyses (ITT). Per-protocol analysis will be conducted separately. Analyses will be computed with an alpha significance level of 5% and two-tailed analyses. Analyses will be performed using IBM SPSS. Comparisons will be computed at a 5% significance level, and BDI II is the primary outcome variable considered as continuous variables. Differences between groups at the posttest will be analysed with a mixed ANOVA having group as the main effect and group *time as an interaction effect. Subgroup analyses will be conducted for anhedonia, apathy, motor imagery, and rumination. F-statistics and p values will be reported for main and interaction effects. The results will be considered as supporting evidence if the F test of the interaction effect is statistically significant (group*time interaction term). Potential mediators of treatment effects will be analysed exploratorily using Hayes model 4 analyses for the primary (depression severity) and secondary outcomes (anhedonia, and apathy). Hayes model 1 will be used to analyse the moderation. Between group effect sizes will be calculated based on Cohen’s d. Treatment completers will be analysed using per protocol analyses. Participants are considered "remitted" if they no longer fulfil the SCID-5 criteria for major depression episodes.

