## Discussion

The study is the first to evaluate an exergame-augmented dynamic imagery intervention added to behavioural activation treatment. It is expected that adding the exergame-augmented dynamic imagery intervention will increase the acceptability of the treatment and decrease the severity of depression, anhedonia, and apathy. We also expect, based on moderation analyses, that this effect to be more pronounced in participants with difficulties of motor imagery at baseline. We further investigate mediators of the treatment effect on the severity of depression and secondary outcomes.

This study is the first to investigate the added benefit of exergame-augmented dynamic motor imagery intervention to behavioural activation treatment. There is an expected advantage that this intervention will make the treatment more accepted (due to XboxKinect^™^) and will overcome the deficiencies in vividness of imagery and the recruitment of motor networks in imagery. If efficient it may work through different mechanisms than the standard BA treatment.

There are several strengths of the study: (1) it is a theory-driven intervention which could show an efficacy advantage, (2) it includes attractive exergames that may show additional benefits (exergame time may be increased and transformed into physical exercise) (3) we included a clinician administered semi-structured interview (SCID-5-CV), (4) we planned for a mid-treatment assessment to evaluate mechanisms of change. At session six, the participants will complete measures of the mechanisms of change, which will be carried out based on temporal precedence criteria [72], (5) assessors are blinded to participants’ treatment conditions.

There are several limitations of the study: (1) it is not a large scale RCT some limitations being related to the small sample size, (2) as the sample size was determined based on post-treatment differences, moderation and mediation analyses being underpowered, (3) participants with high risk of suicide will be excluded based on a score C-SSRS scale [53], limiting the generalisation of the results to participants with high risk of suicide.

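### The stated 90% power is for a posttest two-sample t test, but the trial is decided by the group-by-time interaction F test, for which no power is established

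*Protocol article*

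**What the plan says.** **Sizing.** Protocol article, Proposed sample size: "The sample size was established using G*Power and selecting the difference between two independent means". The assumed effect is a "between-treatment effect size of Cohen’s d = 0.7", and "Forty-four participants per arm will be required to obtain a 90% statistical power". The allowance for loss follows: "Assuming a dropout rate of 20%, 55 patients are required in each treatment arm, resulting in a total of 110 participants". The Discussion, under limitations, confirms which contrast was meant: "the sample size was determined based on post-treatment differences".

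**Decision.** Protocol article, Statistical analyses: BDI-II is the primary outcome, analysed by a mixed ANOVA with group and group-by-time terms. The rule for success is explicit: "The results will be considered as supporting evidence if the F test of the interaction effect is statistically significant". On error rates: "Analyses will be computed with an alpha significance level of 5% and two-tailed analyses".

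**Not given.** The article states no correlation between baseline and later BDI-II scores and no power for the interaction. The analysis section speaks of group differences at posttest, while the abstract lists four assessments (baseline, mid treatment, posttreatment, 3-month follow-up). Which of these enter the ANOVA is not said.

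**The concern.** Both the sizing test and the deciding test are stated, and they are different tests. A two-sample t test at posttest uses the between-person variance of one score. A pre-post interaction uses the variance of the change score, which is larger when the correlation is below 0.5 and smaller when it is above. The same number of patients and the same d therefore give a different power.

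The comparison is active against active, so a non-significant interaction is a realistic outcome. It would be read against a claimed type II error of 10%, and the article gives no basis for that figure on this test. The Discussion names moderation and mediation as the underpowered analyses, which leaves the reader to take the primary test as powered at 90%.

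**Working it through.** **Inputs from the article:** d = 0.7, two-sided alpha 0.05, 44 analysed per arm, 20% dropout, 55 per arm randomised. **Assumptions:** equal SDs at each time, no expected baseline difference, and a range for the baseline-posttest correlation rho.

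**1. The plan's own figure.** Two-sample t test, noncentrality d × sqrt(n/2), df = 2n − 2:
- n = 44: 0.7 × sqrt(22) = 3.28, power 90.1%.
- n = 43: power 89.4%.
- Dropout: 44/0.8 = 55 per arm, 110 in total.

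The figure reproduces, for a posttest t test.

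**2. Pre-post interaction.** With two time points the group-by-time F is the square of a t test on change scores. The variance of change is 2(1 − rho) in units of the score variance, so the effect size is 0.7/sqrt(2(1 − rho)).

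| rho | effect size | power, 44 per arm | power, 55 per arm |
|---|---|---|---|
| 0 | 0.495 | 63% | 73% |
| 0.2 | 0.553 | 73% | 82% |
| 0.3 | 0.592 | 78% | 87% |
| 0.4 | 0.639 | 84% | 91% |
| 0.5 | 0.700 | 90% | 95% |
| 0.6 | 0.783 | 95% | 98% |

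The last column is an upper bound: it treats all 55 randomised per arm as giving full information. At rho = 0.5 the variance factor is 2 × 0.5 = 1, so the two tests have the same power. For 90% power the interaction would need 87, 70, 62, 53 or 44 analysed per arm at rho 0, 0.2, 0.3, 0.4 or 0.5.

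**3. Four time points.** Power then also depends on how the group difference develops. I assumed a correlation of 0.6 among the three later assessments and 44 per arm, and simulated three sets of group differences (in SD, at baseline, mid, post and follow-up): 0, 0.35, 0.7, 0.35; then 0, 0.35, 0.7, 0.7; then 0, 0.7, 0.7, 0.7. Omnibus F without a sphericity correction:
- baseline correlation 0.2: about 66–80%
- baseline correlation 0.3: about 71–85%
- baseline correlation 0.5: about 82–94%

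The low end is the profile that fades at follow-up. A correlation of 0.5 is thus the break-even for the pre-post contrast only.

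**4. Baseline-adjusted posttest contrast.** Effect size 0.7/sqrt(1 − rho²), 44 per arm:
- rho 0.2: 0.714, power 91%
- rho 0.3: 0.734, power 93%
- rho 0.5: 0.808, power 96%

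At rho = 0 the formula gives 90.1%. Simulation with a random baseline covariate gives 89.7%, because estimating a useless covariate costs a little.

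**The case against.** **The shortfall is conditional.** No correlation is given, and at 0.5 or above the pre-post interaction has at least the stated 90%. This stands. A reader might infer that the trial is underpowered, or that power lies at 65–84% for every correlation below 0.5. The documents support neither. Below 0.5 the pre-post range is 63% to just under 90%, and 65–84% is roughly what a four-wave F gives at baseline correlations of 0.2 to 0.3 under assumed profiles. Likewise, a type II error of two to three times the stated 10% holds in the pre-post case at rho 0.2 (27%) and 0.3 (22%), but at 0.4 it is 16%.

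**The entry criterion does not settle the correlation.** One might argue that requiring PHQ-9 of 10 or more narrows the baseline range and lowers rho. That is plausible, but the cut-off is on PHQ-9 while the outcome is BDI-II, and no figure in the article supports a value.

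**Dropouts may contribute.** The plan analyses all randomised patients with multiple imputation, so 44 per arm may be pessimistic. This narrows the concern: with full information from 55 per arm, pre-post power would be 87% at rho 0.3 and 91% at 0.4. It does not remove it, since 44 is the protocol's own basis for the 90%.

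**The trial is a pilot, and its limits are disclosed.** The Discussion says how the sample size was set and lists small size as a limitation. That lowers the severity. It does not tell the reader that the 90% does not carry over to the primary test.

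**Conclusion.** The point holds as a mismatch between the sizing test and the deciding test. It is not an arithmetic error: 44, 55 and 110 are correct for the test that was used. What fails is the transfer of the 90% to the interaction F, for which the article gives no power and no correlation from which to derive it.

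Over the assumed correlations from 0 to 0.6, the power of a pre-post interaction with 44 analysed per arm runs from 63% to 95%. With more time points it also depends on the effect profile. These figures rest on d = 0.7, equal SDs and no expected baseline difference. Whether the trial actually falls short of 90% cannot be decided from the documents. The point should be fixed, but it does not call the trial size itself into question.

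**What to change.** **Preferred.** In Statistical analyses, make the baseline-adjusted (ANCOVA) group difference in BDI-II at posttest the primary test and the success criterion. This matches the section's stated aim of comparing groups at posttest and the basis of the sample size. In Proposed sample size, write that 44 analysed per arm give about 90% power or more at d = 0.7 whatever the baseline correlation (91% at 0.2, 93% at 0.3, 96% at 0.5). The wording should be *about* 90%, because power is a shade under at a correlation of zero.

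**If the interaction F stays primary.** Name the assessments that enter it, state the assumed correlation and effect profile, and replace the 90% with the power of that test, for example about 78% at rho = 0.3 for a pre-post interaction with 44 per arm.

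**Cost.** No added patients under the preferred option. It is more than a wording change in the sample-size section, because it changes the primary test and the success rule, and the interaction F becomes a supporting analysis. The second option changes only the text, but may mean stating a power below 90%.

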### Statistical analyses

Multiple imputation methods will be selected to address the missing data. All randomised patients will be included in intention-to-treat analyses (ITT). Per-protocol analysis will be conducted separately. Analyses will be computed with an alpha significance level of 5% and two-tailed analyses. Analyses will be performed using IBM SPSS. Comparisons will be computed at a 5% significance level, and BDI II is the primary outcome variable considered as continuous variables. Differences between groups at the posttest will be analysed with a mixed ANOVA having group as the main effect and group *time as an interaction effect. Subgroup analyses will be conducted for anhedonia, apathy, motor imagery, and rumination. F-statistics and p values will be reported for main and interaction effects. The results will be considered as supporting evidence if the F test of the interaction effect is statistically significant (group*time interaction term). Potential mediators of treatment effects will be analysed exploratorily using Hayes model 4 analyses for the primary (depression severity) and secondary outcomes (anhedonia, and apathy). Hayes model 1 will be used to analyse the moderation. Between group effect sizes will be calculated based on Cohen’s d. Treatment completers will be analysed using per protocol analyses. Participants are considered "remitted" if they no longer fulfil the SCID-5 criteria for major depression episodes.

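### The primary group-by-time test leaves out baseline BDI-II as a covariate, so it is generally less precise than a baseline-adjusted posttest comparison and is not the test used for sizing

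*Protocol article*

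**What the plan says.** The Statistical analyses section of the protocol article fixes the primary model: "Differences between groups at the posttest will be analysed with a mixed ANOVA having group as the main effect", with group-by-time as the interaction. The same section makes a significant F test of that interaction the criterion for supporting evidence. It names no covariate and does not list the levels of time. The Abstract gives four assessments: baseline, mid treatment, posttreatment and 3 months.

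On error rate and missing data the section says: "Analyses will be computed with an alpha significance level of 5% and two-tailed analyses" and "Multiple imputation methods will be selected to address the missing data".

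The trial was sized on a different test, as its sample-size section shows: "The sample size was established using G*Power and selecting the difference between two independent means". The target set there is 44 analysed per arm for 90% power, and the assumed effect is a "between-treatment effect size of Cohen’s d = 0.7". The Discussion confirms, among the limitations, that sizing rested on post-treatment differences.

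**The concern.** A group-by-time interaction shows a treatment effect by contrasting the group difference at one time with that at another. If only post-baseline visits were levels, a constant benefit would produce no interaction, so baseline is naturally read as one of the levels. Baseline then enters as an outcome, and its noise is carried into the contrast. Using it as a covariate would remove only the part of the posttest variance that it predicts.

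At stake are the power and the confidence-interval width for the primary outcome, in a trial whose Discussion already lists small sample size as a limitation. The stated 90% power also belongs to a test other than the one that decides the result.

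**Working it through.** **Inputs from the protocol article.** Two-sided alpha 0.05 (Statistical analyses); d = 0.7, 44 per arm, 90% power, 20% dropout (Proposed sample size).

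**Assumed, because the documents give no figure.** The correlation rho between baseline and posttest BDI-II, shown from 0.3 to 0.7; the ratio k of baseline SD to posttest SD, shown at 1 and 0.8; d standardised on the posttest SD.

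**Step 1: the plan's own figure.** A two-sample t-test by the noncentral t, with n = 44 per arm, df = 86 and noncentrality 0.7 × sqrt(44/2) = 3.28, gives power 0.901. Dropout: 44/0.8 = 55 per arm, 110 in total. The stated figures reproduce.

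**Step 2: variances, in units of the posttest variance.** With two levels of time, the interaction F is the square of the t statistic on change scores.

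- Change score: 1 + k² − 2·rho·k, which is 2(1 − rho) when k = 1.
- Posttest adjusted for baseline (ANCOVA): 1 − rho².
- Difference: (k − rho)², which is never negative. Apart from one degree of freedom, ANCOVA cannot lose precision on this contrast. The two coincide only when rho = k.

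**Step 3: power at 44 per arm, d = 0.7, k = 1.** The effective effect is 0.7/sqrt(variance), with df 86 for change and 85 for ANCOVA.

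| rho | change variance | ANCOVA variance | power, change | power, ANCOVA |
|---|---|---|---|---|
| 0.3 | 1.40 | 0.91 | 0.783 | 0.926 |
| 0.4 | 1.20 | 0.84 | 0.842 | 0.943 |
| 0.5 | 1.00 | 0.75 | 0.901 | 0.963 |
| 0.6 | 0.80 | 0.64 | 0.953 | 0.982 |
| 0.7 | 0.60 | 0.51 | 0.987 | 0.995 |

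At rho = 0.5 the change variance is 1, so the planned test has exactly the power of the sizing test. Below 0.5 it has less, above 0.5 it has more. ANCOVA has 0.901 even at rho = 0.

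**Step 4: a narrower baseline, k = 0.8.**

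- rho 0.3: change variance 1 + 0.64 − 0.48 = 1.16; power 0.854 vs 0.926.
- rho 0.5: change variance 1 + 0.64 − 0.80 = 0.84; power 0.943 vs 0.963.

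The correlation at which the change test matches the posttest t-test is k/2, here 0.4 instead of 0.5.

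**Step 5: more than two levels of time.** The omnibus F then tests any divergence between the two profiles, not the posttest difference. At 44 per arm, rho = 0.5 and compound symmetry, for assumed standardised differences in visit order:

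- 0, 0.35, 0.7 (three levels): power 0.84
- 0, 0.35, 0.7, 0.7 (four levels): power 0.91
- 0, 0.35, 0.7, 0.35 (four levels, effect fading): power 0.79

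**The case against.** The strongest reply is that nothing here is invalid. Under randomisation the interaction test holds its error rate, and with equal SDs it beats the posttest t-test used for sizing once rho exceeds 0.5. At rho of 0.7 ANCOVA gains less than one percentage point. Eligibility requires a PHQ-9 of 10 or more and a diagnosis, which makes a narrower baseline SD plausible, and that shrinks the gap further. The two-level model is itself inferred. All of this stands. It limits the size of the point, but it does not remove the advantage of adjustment or the mismatch with the sizing test.

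Three stronger readings are tempting, and the documents do not support them.

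- *The F test cannot be combined with multiple imputation.* A two-level interaction is a one-degree-of-freedom contrast that Rubin's rules pool directly, and F statistics can be combined by the D1, D2 or D3 rules. In a simulation (55 per arm, 20% missing, rho 0.5, 20 imputations, 3,000 runs), type I error was 0.051 for the pooled contrast and 0.054 for D2. Simply averaging the F values gave 0.084, but the article does not propose that. A pooling rule is commonly left to an analysis plan, so its absence here is no finding.
- *The group main effect will be taken as a treatment result.* The article does say "F-statistics and p values will be reported for main and interaction effects", but only the interaction is the criterion for supporting evidence.
- *The trial is underpowered.* That would need a known correlation and SD ratio, and the documents give neither.

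**Conclusion.** The point holds as a matter of efficiency and of mismatch with the sample-size calculation. It is not one of bias or invalidity. With baseline and posttest as the two levels, the planned test has 78% to 99% power at 44 per arm as rho runs from 0.3 to 0.7 with equal SDs, against 93% to 99.5% for ANCOVA. The loss is material at low to moderate rho and negligible near 0.7; with a baseline SD 0.8 of the posttest SD it is about half as large or less. Under the planned test the stated 90% therefore rests on a correlation and an SD ratio that are stated nowhere, whereas ANCOVA gives about 90% or more at any rho. If time has three or four levels, these two-level figures do not apply, and power depends on the pattern of effects over visits. The change is worth making because it is nearly free, though its benefit in this trial cannot be fixed from the documents.

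**What to change.** Make the primary analysis the between-group difference in posttest BDI-II, adjusted for baseline BDI-II by ANCOVA. Pool the group coefficient and its standard error across imputations by Rubin's rules and report the estimate with a 95% CI. Base the criterion for supporting evidence on that coefficient. Treat the continuous secondary outcomes in the same way, each adjusted for its own baseline.

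A likelihood-based linear mixed model on the post-baseline visits, with baseline BDI-II as covariate and a prespecified posttest contrast, is an alternative. It is not equivalent: it uses more visits and handles missing values through the likelihood, so it would replace the planned imputation. One of the two should be named as primary.

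If the mixed ANOVA is kept, list the levels of time and state the correlation and SD ratio under which it reaches 90% power.

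The cost is a change of wording before the data are analysed. It needs no new patients or measurements, since BDI-II is already collected at baseline. The sample size can stay: 44 analysed per arm gives ANCOVA about 90% power even if baseline predicts nothing.

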**Methods and analyses:**

In a two-arm pilot randomised controlled trial, the acceptability and preliminary efficacy of an exergame-augmented dynamic imagery intervention added to behavioural activation treatment for depressed individuals will be assessed. Participants (age 18–65) meeting criteria for depression are recruited by media and local announcements. 110 participants will be randomly allocated to behavioural activation plus imagery group or to standard behavioural activation group. The primary outcome is depressive symptom severity (Beck Depression Inventory II) and secondary outcomes are anhedonia, apathy and behavioural activation and avoidance. The outcomes are assessed at baseline, mid treatment, posttreatment and 3-month follow-up. Moderation and mediation analyses will be explored. An intention-to-treat approach with additional per-protocol analysis will be used for data analysis.

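### The success rule is a group*time F test with no time levels, decisive contrast or direction, although the question and the sample size concern the posttest difference in BDI-II

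*Protocol article*

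**What the plan says.** The Statistical analyses section names BDI-II as the primary outcome and introduces the model with a posttest aim: "Differences between groups at the posttest will be analysed with a mixed ANOVA". Its terms are group and the interaction of group with time. The decision rule follows a few sentences later: "The results will be considered as supporting evidence if the F test of the interaction effect is statistically significant". The interaction meant is group by time. Testing is two-tailed at 5%. Between-group Cohen's d will be calculated, but it is not part of the rule and no time point is given for it. The levels of time are not listed.

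On timing, the Abstract states: "The outcomes are assessed at baseline, mid treatment, posttreatment and 3-month follow-up". The Study design section adds weekly assessments and describes the week-six assessment as one of mediators.

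On size, the Proposed sample size section uses a comparison of two independent means with d = 0.7 and 90% power. This gives 44 per arm, or 55 per arm (110 in total) after 20% dropout. The Discussion confirms the time point: "as the sample size was determined based on post-treatment differences". The hypothesis at the end of the Introduction is directional: the added imagery is expected to strengthen the effect of BA on depressive symptoms.

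**The concern.** The question, the sample size and the decision rule should point at the same quantity. Here the first two point at the between-arm difference at posttest. The rule points at an interaction term whose meaning depends on which occasions are in the model, and the article does not say which.

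With more than two occasions, a significant group*time F test shows only that the difference between arms is not constant over time. It does not say when the arms differ or which arm does better. The trial could then meet its stated criterion with no posttest difference at all, and the time point used to explain the result could be chosen after the data are seen. The sentence governs the trial's main efficacy conclusion.

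**Working it through.** **Inputs from the article.** Two-sided alpha 0.05; d = 0.7; 44 analysed per arm; 55 per arm randomised; four outcome occasions (baseline, mid-treatment, posttreatment, 3 months).

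**Assumptions not in the article.** Compound symmetry; SD 1 at each occasion; no baseline difference; within-person correlation rho of 0.3, 0.5 or 0.7.

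**Step 1: the plan's own figure.** For a two-sample t test with n = 44 per arm, df = 86 and noncentrality 0.7 × √(44/2) = 3.28. Power is 90.1%; with 43 per arm it is 89.4%. So 44 is right, and 44/0.8 = 55 per arm, 110 in total. The stated size reproduces, as a posttest two-mean comparison.

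**Step 2: the rule with four time levels.** Let δ_t be the between-arm difference in SD at occasion t and δ̄ its mean. The F test has 3 and 3 × 86 = 258 df and noncentrality

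λ = (n/2) × Σ(δ_t − δ̄)² / (1 − rho).

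For a difference at mid-treatment only, (0, 0.7, 0, 0), δ̄ = 0.175 and Σ(δ_t − δ̄)² = 0.525² + 3 × 0.175² = 0.3675. With n/2 = 22, λ = 8.085/(1 − rho), which is 11.55, 16.17 and 26.95. A difference at follow-up only gives the same sum.

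| Profile in SD (baseline, mid, post, 3 months) | Σ(δ_t − δ̄)² | rho 0.3 | rho 0.5 | rho 0.7 |
|---|---|---|---|---|
| Mid only (0, 0.7, 0, 0) | 0.3675 | 82% | 93% | 99.6% |
| Follow-up only (0, 0, 0, 0.7) | 0.3675 | 82% | 93% | 99.6% |
| Gradual and held (0, 0.35, 0.7, 0.7) | 0.3369 | 78% | 91% | 99% |
| Posttest effect that halves (0, 0.35, 0.7, 0.35) | 0.2450 | 63% | 79% | 96% |

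The first two rows have no posttest difference, yet they meet the rule at least as often as the third row, which is a real and lasting posttest benefit.

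**Step 3: the rule with two time levels (baseline, posttest).** The test has 1 and 86 df. For (0, 0.7), Σ(δ_t − δ̄)² = 0.245 and power is 78%, 90% and 99%. A difference confined to mid-treatment or follow-up does not enter the test.

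**Step 4: a posttest contrast instead.** Unadjusted, 44 per arm gives the 90.1% of Step 1. With adjustment for baseline, the effect in residual SD units is 0.7/√(1 − rho²), and power is 93%, 96% and 99.5% at rho 0.3, 0.5 and 0.7. With the requirement that the difference favour BA plus T-RAC, the chance of declaring support when there is no effect is 2.5%.

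**The case against.** The strongest reply is that the 3-df test is not stated. The model sentence begins "Differences between groups at the posttest will be analysed with a mixed ANOVA", which can be read as a baseline-to-posttest comparison. The Abstract gives a measurement schedule, not a model specification, and the article ties the mid-treatment assessment to mechanisms of change. This stands: the four-occasion reading is the natural one, but the transient and late scenarios depend on it. The mid-only profile is also an extreme, chosen to show what the test responds to.

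A reader might infer that the rule would declare success for a harmful result. The documents do not support making that a main charge. Any two-sided test rejects equally often for mirror-image effects, so quoting its power with the sign flipped shows nothing special about this rule. The hypothesis is directional, and the means and Cohen's d will show the sign. What stands is that the sentence omits a phrase requiring the expected direction.

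A reader might also infer that the F test is less powerful than the planned t test. That is not general. For an effect that halves by follow-up, power is below 90% at rho 0.3 and 0.5 but 96% at rho 0.7.

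Finally, a condensed article may leave time levels and follow-up contrasts to a fuller document. That would excuse silence. It does not excuse a decision rule that the article itself states and that does not match its own question.

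**Conclusion.** The concern holds in a conditional form. As written, the success rule is not tied to the posttest difference that the trial is about and was sized for, and the article allows two readings that give different primary tests.

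- **Four occasions in the model:** a 0.7 SD difference absent at posttest meets the rule in 82%, 93% and 99.6% of trials at rho 0.3, 0.5 and 0.7, given 44 per arm and compound symmetry.
- **Baseline and posttest only:** this problem vanishes, and only the minor omission of direction is left.

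The fault is in the wording of the rule. Alpha and the sample size are not affected, and the sample-size arithmetic is correct. The article does not establish that the investigators would report a harmful or purely transient effect as success; the written rule simply does not rule out the transient or late case on the natural reading.

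**What to change.** Replace the decision sentence with wording such as: *The primary test is the between-arm difference in BDI-II at posttest, adjusted for baseline BDI-II (1 df, two-sided 5%), reported with its estimate and 95% confidence interval. Efficacy is supported only if this difference is statistically significant and favours BA plus T-RAC. The between-arm difference at 3 months is a secondary analysis. The overall group*time F test is descriptive.* List the occasions that enter the mixed model in the same paragraph.

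The cost is one or two sentences, with no new data and no change to the 44 evaluable per arm or 110 randomised. The one real downside is that an effect seen only at follow-up becomes a secondary result.
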